## Abstract

**Background:**

After receiving breast cancer surgery or reconstruction, shoulder dysfunctions including weakness, post-operative pain, shoulder joint instability, and limited range of motion (ROM) often occur. Due to limited ROM, patients may suffer difficulty in activities of daily living, and quality of life may be reduced. The objective of this study is to compare the effects on shoulder ROM of a real-time interactive digital healthcare system and brochure-based home rehabilitation program in post-operative breast cancer patients.

**Methods:**

This study is a prospective, multi-center, assessor-blinded randomized controlled trial. The study aims to recruit 100 breast cancer patients exhibiting limited shoulder ROM after undergoing axillary lymph node dissection or breast reconstruction following mastectomy. Patients will be randomly assigned to two groups for 8 weeks of rehabilitation: a digital healthcare system rehabilitation (intervention) group and a brochure-based rehabilitation (control) group. The primary outcome is the change in ROM of the affected shoulder between baseline and 12 weeks after enrollment. Secondary outcomes include pain in the affected shoulder, as measured using a numerical rating scale, functional outcomes (QuickDASH scores), and quality of life (FACT-B and EQ-5D-5L scores), all of which will be measured on enrollment and 4, 8, and 12 weeks thereafter.

**Discussion:**

This study will compare the effectiveness of a newly developed, augmented reality-based real-time interactive digital healthcare system with that of brochure-based home rehabilitation for improving the shoulder ROM, pain, functional outcomes, and quality of life of post-operative breast cancer patients.

**Trial registration:**

ClinicalTrials.govNCT04316156. Registered on 20 March 2020.

**Supplementary Information:**

The online version contains supplementary material available at 10.1186/s13063-021-05535-8.

## Background

Breast cancer is one of the most common forms of cancer, and cancer death, among females; it accounted for 11.6% of the 18.1 million new cancer cases worldwide in 2018 [1]. Shoulder disabilities frequently occur following breast cancer surgery, especially after axillary lymph node dissection (ALND) and mastectomy [2–6]. Weakness, lymphedema, limited range of motion (ROM), and pain in the upper extremity on the operated side are common symptoms [3, 4]. After mastectomy, several reconstruction methods are commonly considered, such as expander/implant-based reconstruction and autologous reconstruction using abdominal tissue or latissimus dorsi muscle. Decreased strength of the affected upper limb, reduced shoulder joint stability and shoulder ROM, and functional limitations may arise after breast cancer reconstruction [7, 8]. Due to these postsurgical complications, which are also associated with emotional changes, a high proportion of patients complain of decreased quality of life and difficulty performing daily activities [4, 8–10].

Exercise is reportedly effective for improving shoulder dysfunction and quality of life after breast cancer surgery. After ALND, participants who received physical therapy and posture education showed improvement in postsurgical shoulder pain and the ability to perform daily activities [9]. Shoulder function and health-related quality of life also significantly improved after upper limb exercises and muscle relaxation training [11]. Furthermore, early rehabilitation, including shoulder ROM and strengthening exercises, improved shoulder ROM after breast cancer surgery [12].

Recently, new technologies facilitating rehabilitation, such as virtual reality (VR) and augmented reality (AR), have been introduced. One study examined the effectiveness of VR-based Xbox Kinect (Microsoft Corp., Redmond, WA, USA) games for rehabilitating breast cancer patients after surgery [13]. To our knowledge, however, outcomes of real-time interactive AR-based rehabilitation programs for breast cancer surgery patients have not yet been reported. Therefore, we aimed to investigate the usefulness of AR system for shoulder dysfunction in post-operative breast cancer patients.

The primary objective of this prospective randomized controlled study is to compare the effectiveness of an AR-based digital healthcare system using motion sensors with that of brochure-based home rehabilitation for shoulder ROM after breast cancer surgery. The study protocol is reported according to the Standard Protocol Items: Recommendations for Interventional Trials (SPIRIT) guidelines (Additional file 1); a schematic is provided in Fig. 1.

**Fig. 1 Fig1:**
[figure not shown]
The schedule of enrollment, interventions, and assessments

## Methods/design

### Study design and setting

This is a prospective, multi-center, assessor-blinded randomized controlled study. Breast cancer patients who underwent breast cancer surgery in two university hospitals in South Korea (Samsung Medical Center, Sungkyunkwan University School of Medicine and Seoul St. Mary’s Hospital, College of Medicine, The Catholic University of Korea) will be recruited. The enrolled participants will be randomly allocated to either the digital healthcare rehabilitation group or the brochure-based rehabilitation group. Both groups will receive rehabilitation for 8 weeks. A flowchart of the study design is shown in Fig. 2.

**Fig. 2 Fig2:**
[figure not shown]
Flowchart of the study

### Randomization, allocation concealment, and blinding

Participants meeting the eligibility criteria will be randomly assigned to either the digital healthcare or brochure-based rehabilitation group, in a 1:1 ratio using a block randomization procedure through computer-generated sequences with block size of four. One research team member will independently allocate the participants to groups using the sequences generated by computer. The researchers involved in the randomization process will not participate in the enrollment and assessment processes, and the allocation will be concealed by sealed notes. Therefore, both the participants and researchers involved in enrollment and assessment will be blinded to the allocation process. An experienced physical or occupational therapist blinded to the group allocations will assess the primary outcome.

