### Intervention

#### Digital healthcare system (intervention) group

In the intervention group, rehabilitation will be provided via the UINCARE Home+ rehabilitation system (UINCARE Corp., Seoul, Korea), which will be delivered to the participants after enrollment. The UINCARE Home+ is based on infrared technology and includes an Xbox One Kinect for Windows® (Microsoft Corp.) motion capture device. It provides real-time feedback directly to the user by tracking the movements of 25 joints, in both the upper and lower extremities, in three-dimensional space. Physicians can prescribe exercise to the user through the Internet. Task performance, including repetitions and movement accuracy, is recorded in real time.

After logging in to the UINCARE Home+ system, participants can perform daily exercises, as prescribed by the physician. The exercise program consists of two components, with two levels each (total of four levels). After performing the exercises of a given level for 2 weeks, the participant progresses to the next level. At a follow-up assessment 4 weeks after enrollment, the program may be recalibrated by the physician. If the participant experiences difficulty performing the exercises at one level, that level will be maintained for a further 2 weeks. The entire exercise program is shown in Table 1. Each session comprises 12–14 workouts, with a 2.5-min warm-up period and 45-s cool-down period. The total session length is approximately 30 min. Each workout is repeated five times, and participants will be asked to perform an exercise session more than once a day on every day of the week. The exercise program will be performed over 8 weeks.

**Table 1 Tab1:** The entire exercise program

	Part 1 (level 1)	Part 1 (level 2)	Part 2 (level 3)	Part 2 (Level 4)
Warm up	Deep breathing Trunk twist (Rt./Lt.)	Deep breathing Trunk twist (Rt./Lt.)	Deep breathing Trunk twist (Rt./Lt.)	Deep breathing Trunk twist (Rt./Lt.)

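### A single, disclosed block size of four in a trial with openly distinguishable arms lets up to one allocation in three be deduced by an enroller who knows the earlier ones

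*Protocol article*

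**What the plan says.** The section on randomization, allocation concealment and blinding sets allocation "in a 1:1 ratio using a block randomization procedure through computer-generated sequences with block size of four". On procedure it says "One research team member will independently allocate the participants to groups using the sequences generated by computer". It adds that the researchers who randomise "will not participate in the enrollment and assessment processes, and the allocation will be concealed by sealed notes", and concludes that "both the participants and researchers involved in enrollment and assessment will be blinded to the allocation process". Of the outcome assessor it says something stronger: "An experienced physical or occupational therapist blinded to the group allocations will assess the primary outcome".

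The intervention sections show that the arms differ visibly after enrolment. The digital system is a physical device, "which will be delivered to the participants after enrollment", and "Physicians can prescribe exercise to the user through the Internet". Control patients receive a brochure and exercise log books. In both arms the exercise level can be reset at the 4-week visit.

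Recruitment is from "two university hospitals in South Korea". Planned enrolment is 100, which is 25 blocks of four if one list is used. The trial status section gives a recruitment start of 16 April 2020 and expected completion in June 2022.

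**The concern.** Concealment has two parts. The next assignment must not be readable in advance, and it must not be deducible from earlier assignments. Sealed notes and a separate randomiser deal with the first. The second depends on the block design and on what enrolling staff know about past patients. With one constant block size known to all, anyone who follows the arms given out so far can tell when a block has used up its two places in one arm.

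The stated safeguard for enrolling staff is blinding to the allocation process. Only the therapist who measures the primary outcome is said to be blinded to group. The staff who prescribe on the digital system necessarily know who has it. The article does not say whether any of them also enrol patients.

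What is at stake is selection bias. Patients may enter at any time up to 8 weeks after surgery, after different operations, and with any flexion or abduction below 160°. This leaves an enroller some latitude over whom to approach and when. The primary outcome is change in range of motion from baseline, compared by a t test or Mann–Whitney test. Any steering by expected recovery would pass directly into the estimate, and a blinded assessor cannot remove it.

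**Working it through.** **Inputs.** From the randomization section: 1:1 ratio, block size 4. From the sample size section: 100 patients. Assumed, because the article does not give them: what an enroller can see, and each hospital's share of a shared list.

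**The plan's own figures.** The article states no predictability figure. Its sample size reproduces: 2 × (23 × (1.960 + 0.842)/15)² = 36.9, rounded up to 37 per group; 37/0.80 = 46.25, rounded up to 47. This point does not affect it.

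**1. Upper bound: block starts and all earlier allocations known.** A block has six equally likely orders of two A and two B.

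| Position in block | Probability that the arm is certain | Probability that the best guess is right |
|---|---|---|
| 1 | 0 | 1/2 |
| 2 | 0 | 2/3 |
| 3 | 1/3 (first two alike: 2 of 6 orders) | 1/3 × 1 + 2/3 × 1/2 = 2/3 |
| 4 | 1 | 1 |

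- Certain: (1/3 + 1)/4 = 1/3 = 33.3%. Over 25 blocks this is 25 × 4/3, about 33 of 100 patients.
- Best guess right: (1/2 + 2/3 + 2/3 + 1)/4 = 17/24 = 70.8%, against 50% by chance.

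**2. One list shared by both hospitals, only own-site arms seen.** Let p be the share of the list that goes to the enroller's hospital, and suppose the enroller still knows the list position of each own patient. Position 3 is certain only if the first two patients are both own-site and in the same arm: p²/3. Position 4 is certain only if both earlier patients in the opposite arm are own-site: p². The certain share is (p²/3 + p²)/4 = p²/3. Simulation gave the same values.

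| Assumed share p | Certain | Best guess right |
|---|---|---|
| 90% | 27% | 68% |
| 70% | 16% | 64% |
| 50% | 8% | 60% |
| 30% | 3% | not calculated |

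An enroller who did not know list positions would do worse than this.

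**3. Randomly varying block sizes.** These are simulated lists of 100, with an observer who sees every earlier arm and knows the set of sizes but not which size is in use:

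- sizes 4 and 6: 5.6% certain
- sizes 2, 4 and 6: 4.0%
- sizes 4, 6 and 8: 2.4%

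Simply enlarging a fixed block helps much less. A fixed block of 6 leaves 25% certain and the best guess right 68.3% of the time; a fixed block of 8 leaves 20% and 66.6%.

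**The case against.** The strongest reply is that prediction needs one person who enrols patients, learns every earlier arm on the list and knows where blocks start, and the article describes no such person. Randomising staff are kept out of enrolment and assessment, allocation is in sealed notes, the outcome assessor is blinded, and the device goes to the patient. The prescribing physician knows the arm, but nothing says that this physician enrols. A fixed block of four is also a legitimate method, and the section contains no miscalculation.

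Most of this stands. A reader might infer that recruiting staff see each patient's arm and that one allocation in three is therefore known in this trial. The documents do not support that: they neither state nor exclude that enrollers learn earlier arms. What the reply does not remove is that the listed safeguards do not prevent inference from past allocations, and that no statement keeps enrolling staff from learning them.

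A reader might also infer that the randomization wrongly omits hospital as a stratum, or that the analysis wrongly omits it as a covariate. That is not supported either. The article is condensed, speaks of sequences in the plural and does not exclude a list per hospital; such details may sit in the full protocol or analysis plan. Nor does it document any difference in surgical mix between the hospitals. The two complaints would also pull against each other: the one-third figure applies where an enroller sees the whole list, as with a list per hospital, while a shared list lowers predictability for staff who see only their own site.

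**Conclusion.** The point holds as a design weakness that is cheap to close. It is not a contradiction, and it is not evidence of bias. With the stated fixed block of four, at most 33.3% of allocations are certain and the best guess is right at most 70.8% of the time. Both limits assume that the enroller knows the block starts and all earlier allocations on the list. For a shared list with only own-site arms visible, certainty is about 3% to 27% over assumed hospital shares of 30% to 90%, and about 8% at 50:50. If enrolling staff learn no earlier arms, the exposure is nil. The documents do not show which case applies, and no bias in degrees of motion can be derived from them.

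**What to change.** For patients still to be randomised, generate new sequences by computer with randomly varying block sizes, for example 4 and 6, and do not disclose the sizes to recruiting staff. Add a sentence to the randomization section that recruiting staff are kept unaware of earlier allocations where feasible. Under the full-knowledge assumption, sizes 4 and 6 bring the certain share from 33.3% down to about 5.6%, even if the set of sizes becomes known. Better-than-chance guessing is not abolished, so the second sentence matters as well as the first.

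The cost is a new sequence, new sealed notes and a short amendment reported to the review board; the trial status section currently says no change is planned. Sample size is unchanged. Arm sizes may no longer end at exactly 50 and 50: stopping inside a block of 6 can leave a difference of up to 3 patients per list. The block of four in use at the changeover should be completed first, or it can add up to 2 more.

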### Intervention

#### Digital healthcare system (intervention) group

In the intervention group, rehabilitation will be provided via the UINCARE Home+ rehabilitation system (UINCARE Corp., Seoul, Korea), which will be delivered to the participants after enrollment. The UINCARE Home+ is based on infrared technology and includes an Xbox One Kinect for Windows® (Microsoft Corp.) motion capture device. It provides real-time feedback directly to the user by tracking the movements of 25 joints, in both the upper and lower extremities, in three-dimensional space. Physicians can prescribe exercise to the user through the Internet. Task performance, including repetitions and movement accuracy, is recorded in real time.

After logging in to the UINCARE Home+ system, participants can perform daily exercises, as prescribed by the physician. The exercise program consists of two components, with two levels each (total of four levels). After performing the exercises of a given level for 2 weeks, the participant progresses to the next level. At a follow-up assessment 4 weeks after enrollment, the program may be recalibrated by the physician. If the participant experiences difficulty performing the exercises at one level, that level will be maintained for a further 2 weeks. The entire exercise program is shown in Table 1. Each session comprises 12–14 workouts, with a 2.5-min warm-up period and 45-s cool-down period. The total session length is approximately 30 min. Each workout is repeated five times, and participants will be asked to perform an exercise session more than once a day on every day of the week. The exercise program will be performed over 8 weeks.

**Table 1 Tab1:** The entire exercise program

	Part 1 (level 1)	Part 1 (level 2)	Part 2 (level 3)	Part 2 (Level 4)
Warm up	Deep breathing Trunk twist (Rt./Lt.)	Deep breathing Trunk twist (Rt./Lt.)	Deep breathing Trunk twist (Rt./Lt.)	Deep breathing Trunk twist (Rt./Lt.)
Main workout	Passive forward flexion 90° Passive external rotation 45° Passive abduction 90° Trunk rotation with both shoulder forward flexion 90° (Rt./Lt.) Active forward flexion 90° Active abduction 90° (both arm) Passive forward flexion 90° Passive external rotation 45° Passive abduction 90° Trunk rotation with both shoulder forward flexion 90° (Rt./Lt.) Active forward flexion 90° Active abduction 90° (both arm)	Passive forward flexion 180° Passive external rotation 90° Passive abduction 180° Active forward flexion 180° Active abduction 180° Active external rotation Pectoralis stretching^a^ Passive forward flexion 180° Passive external rotation 90° Passive abduction 180° Active forward flexion 180° Active abduction 180° Active external rotation Pectoralis stretching^a^	Passive forward flexion 180° Passive external rotation 90° Passive abduction 180° Forward flexion 90° with dumbbell Abduction 90° with dumbbell Pectoralis stretching^b^ Active forward flexion 180° Active abduction 180° Active external rotation 90° Forward flexion 90° with dumbbell Abduction 90° with dumbbell Pectoralis stretching^b^	Active forward flexion 180° Active abduction 180° Active external rotation 90° Forward flexion 180° with dumbbell Abduction 180° with dumbbell External rotation with dumbbell Biceps strengthening with dumbbell Pectoralis stretching^c^ Forward flexion 180° with dumbbell Abduction 180° with dumbbell External rotation with dumbbell Pectoralis stretching^c^
Cool down	Deep breathing	Deep breathing	Deep breathing	Deep breathing

^a^Pectoralis stretching is performed with both arms abducted

^b^Pectoralis stretching is performed with interlocking fingers behind the back and raising both arms up

^c^Pectoralis stretching is performed with interlocking fingers behind the occiput and moving both elbows backward

#### Brochure-based home rehabilitation (control) group

Participants allocated to the control group will receive a brochure detailing the same exercise program followed by the intervention group (Table 1). The brochure contains pictures and brief written summaries of each motion. Similar to the intervention group, the brochure-based home rehabilitation group will be assessed at a 4-week follow-up, and the level of exercise will be set according to the results of that assessment. The control group will also be asked to perform exercise sessions more than once a day on every day of the week. Adherence to the exercise program will be monitored using exercise log books, which will be provided at enrollment and the 4-week follow-up.

### Outcome measures

The primary outcome of the study is the change in ROM (flexion or abduction) in the affected shoulder between baseline and 12 weeks. Flexion, abduction, external rotation, and internal rotation will be measured both passively and actively in a sitting position. External and internal rotation will be measured with the shoulder abducted to 90° or as much as possible. ROM will be measured using a goniometer. Measurements will be performed on enrollment, and 4, 8, and 12 weeks thereafter, by a physical or occupational therapist blinded to the group assignments.

The secondary outcomes of this study are pain, functional outcomes, and quality of life. The intensity of pain in the affected shoulder will be measured using a numerical rating scale (NRS), which is a simple and commonly used method for rating pain intensity from 0 (*no pain*) to 10 (*worst pain imaginable*) [14]. Both maximum pain and general pain will be measured at each visit: maximum pain refers to the most intense pain experienced during the week before the visit, and general pain represents the average pain intensity during that week. Functional outcomes will be measured using the short-form version of the Disabilities of the Arm, Shoulder and Hand questionnaire (QuickDASH), a widely used self-report measure of upper extremity disability [15]. Higher QuickDASH scores reflect poorer functional outcomes. Quality of life will be measured using the Functional Assessment of Cancer Therapy-Breast (FACT-B) and EuroQol Five-dimensional (EQ-5D-5L) instruments. The FACT-B scale consists of 37 items and is specifically aimed at breast cancer patients. The four subdomains of FACT-B are physical, social/family, emotional, and functional well-being. Higher FACT-B scores reflect better the quality of life [16–18]. The EQ-5D-5L questionnaire captures health status based on five dimensions: mobility, self-care, usual activities, pain/discomfort, and anxiety/depression [19]. Each dimension is scored from 1 to 5, and health status is summarized as a five-digit code: “11111” represents no problems in any of the five dimensions, and “55555” represents the worst possible health status. Higher EQ-5D-5L scores indicate better health status [20]. Secondary outcomes will also be assessed, on enrollment and 4, 8, and 12 weeks thereafter. Time schedule of enrollment, interventions, assessments are presented in Fig. 1.

### Statistical analysis

#### Sample size

The standard deviation of ROM in the affected shoulder is expected to be 23°, and the difference in ROM between groups is expected to be 15° based on a previous study [9] and our own unpublished preliminary study. Using two-sample *Z* tests, and assuming homogeneity of variance, the sample size was estimated at 37 for each group with an alpha level of 5% and power of 80%. With an expected dropout rates of 20%, at least 47 participants are needed in each group, so enrollment of 100 participants (*n* = 50 per group) is planned.

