#### Data analysis

All statistical analyses will be performed using SPSS® Statistics (version 24.0; IBM Corp., Armonk, NY, USA). The Shapiro–Wilk test will be used to evaluate the normality of the data. The primary outcome will be analyzed using the independent *t* test or Mann–Whitney test, depending on the normality of the data. The secondary outcomes will be analyzed using a linear mixed model or generalized estimating equation. *P* values < 0.05 will be considered statistically significant. Both intention to treat and per protocol analyses will be performed.

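### The sample size uses an SD of ROM but the primary test is an unadjusted comparison of change in ROM, so the 80% power claim is unsupported; baseline-adjusted ANCOVA is at least as powerful under either reading of the 23° and needs no extra data

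*Protocol article*

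**What the plan says.** Three places in the protocol article bear on this point.

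- **Sample size.** "The standard deviation of ROM in the affected shoulder is expected to be 23" degrees, and "the difference in ROM between groups is expected to be 15" degrees. Both are worded as ROM, not as change in ROM. They are attributed to a previous study and to unpublished preliminary work by the investigators. With a two-sample Z test, "assuming homogeneity of variance", "the sample size was estimated at 37 for each group" "with an alpha level of 5% and power of 80"%. Then: "With an expected dropout rates of 20%, at least 47 participants are needed in each group", and 50 per group are to be enrolled.
- **Outcome measures.** The primary outcome is "the change in ROM (flexion or abduction) in the affected shoulder between baseline and 12 weeks".
- **Data analysis.** "The primary outcome will be analyzed using the independent" t test, or the Mann–Whitney test if the data are not normal. Neither uses baseline ROM as a covariate.

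The article gives no correlation between baseline and week-12 ROM. It does not say whether 23° belongs to one visit (or which visit) or to the change.

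**The concern.** The power of a two-group test depends on the SD of the quantity tested. Here that quantity is a change score, while the planning SD is described as that of ROM. The two agree only under a particular correlation between visits. If ROM has the same SD at both visits, the change is more variable than ROM itself whenever that correlation is below 0.5. An unadjusted change-score test then has less power than a calculation based on the visit SD suggests.

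A modest correlation is conceivable. Under Eligibility criteria, patients may enter at any time up to 8 weeks after surgery, following either axillary dissection or reconstruction. Baseline ROM may therefore partly reflect time since surgery, and the final measurement comes 12 weeks later.

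Two things are at stake: whether the stated power belongs to the stated analysis, and whether the analysis leaves precision unused. Baseline ROM is measured in every patient, but enters the primary test only by subtraction.

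**Working it through.** **Inputs from the Sample size section:** SD 23°, difference 15°, alpha 5% (taken as two-sided, which reproduces the stated n), power 80%, dropout 20%, 50 enrolled per group. Completers per group: 50 × 0.8 = 40.

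**Assumed input:** rho, the correlation between baseline and week-12 ROM. The article gives none, so a range is shown.

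**Step 1. Reproduce the plan.**
- n per group = 2 × (1.960 + 0.842)² × 23² / 15² = 36.9, rounded up to 37.
- 37 / 0.8 = 46.25, rounded up to 47.

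Both stated figures reproduce, so the arithmetic is sound. The question is what the 23° describes.

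**Step 2. Reading A: 23° is the SD at a visit, equal at baseline and week 12.**
- SD of change = 23 × √(2(1 − rho))
- Residual SD after adjusting for baseline (ANCOVA) = 23 × √(1 − rho²)

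Power for a 15° difference with 40 per group, from the noncentral t distribution (one degree of freedom fewer for ANCOVA):

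| rho (assumed) | SD of change | Power, change-score t test | ANCOVA SD | Power, ANCOVA |
|---|---|---|---|---|
| 0.2 | 29.1° | 62% | 22.5° | 84% |
| 0.3 | 27.2° | 68% | 21.9° | 86% |
| 0.4 | 25.2° | 75% | 21.1° | 88% |
| 0.5 | 23.0° | 82% | 19.9° | 91% |
| 0.6 | 20.6° | 90% | 18.4° | 95% |

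The change-score test reaches 80% power at rho = 0.51 with 37 per group and at rho = 0.47 with 40 per group. At rho = 0.3 it needs 53 completers per group, against the planned 37.

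**Step 3. Reading B: 23° is the SD of the change.** The calculation then matches the test: power is 79% at 37 per group by the t test (80% by the Z test used in the plan) and 82% at 40. With equal visit SDs, the visit SD implied by a change SD of 23° is 23 / √(2(1 − rho)). The ANCOVA residual SD is therefore 23 × √((1 + rho)/2):
- rho 0.7: 21.2°, power 88%
- rho 0.5: 19.9°, power 91%
- rho 0.3: 18.5°, power 95%

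**Step 4. Is ANCOVA ever worse?** The change score is the week-12 value minus 1 × baseline. ANCOVA estimates the slope instead of fixing it at 1, so its residual variance cannot exceed the variance of the change, even with unequal visit SDs. The only price is one degree of freedom.

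**Step 5. Unequal visit SDs.** Under Reading A with 23° as the week-12 SD, the break-even correlation for matching that SD is SD(baseline) / (2 × SD(week 12)). This is 0.375 if the baseline SD is 75% of the week-12 SD, and 0.75 if it is 150%. With assumed SDs of 17.25° at baseline and 23° at week 12, the change-score test at 40 per group has 78% power at rho 0.3 and 84% at rho 0.4.

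**The case against.** The strongest reply is that no shortfall has been shown. It requires 23° to be a single-visit SD and rho to be low, and the article establishes neither. In a condensed article whose endpoint is change in ROM, ROM in the Sample size section may be shorthand for change in ROM. The calculation would then fit the test. This stands, and it is why the point concerns an unsupported power claim.

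Three stronger readings are tempting, and the document supports none of them.

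- **That the trial is underpowered.** At rho of about 0.5 or more, or under Reading B, power is adequate as planned.
- **That the entry criterion truncates baseline and so forces a low rho.** Eligibility requires limitation in flexion or in abduction, so a patient may qualify on one movement and have 160° or more on the other. The movement analysed need not be truncated. Truncation would also tend to shrink the baseline SD, which lowers the break-even correlation (Step 5).
- **That ANCOVA secures 80% power whatever rho is.** This holds only if 23° is the week-12 SD. If 23° were the baseline SD and the week-12 SD were 28.75° (assumed), ANCOVA at 40 per group would have 68% power at rho 0.3.

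It is also fair to say that validity is not at issue. Under randomisation the change-score t test is unbiased with the right type I error, so ANCOVA is a gain in efficiency. Adjustment for hospital is optional, since the article describes no stratification by hospital. Finally, Trial status describes the protocol as final with recruitment under way, so the change is an amendment and not merely an edit.

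None of this removes the mismatch between the planning SD and the tested quantity. Nor does it give a reason to prefer the unadjusted test, since ANCOVA is at least as powerful under either reading, apart from the one degree of freedom.

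**Conclusion.** The point holds in conditional form. The SD is described for ROM, the test is on change in ROM without baseline adjustment, and nothing in the article links the two, so the 80% power claim is unsupported.

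Its possible size depends on what 23° means. As a visit SD, equal at both visits, it leaves the planned test with about 62% to 75% power for assumed rho of 0.2 to 0.4 with 40 completers per group; ANCOVA would have 84% to 88%. As the SD of change, it leaves the planned test with 82%, and ANCOVA would raise this to about 88–95% for rho from 0.7 down to 0.3. All rho values are assumptions. The planned test is less efficient, not biased. The case for changing it is that the baseline data are already collected and adjustment helps under both readings.

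**What to change.** - **Data analysis.** Before any unblinded analysis, replace the choice between t test and Mann–Whitney test with an ANCOVA of week-12 ROM on treatment and baseline ROM of the same movement. Using change as the response gives the same treatment estimate when baseline is in the model. Hospital may be added as a covariate. Report the adjusted mean difference in degrees with its 95% confidence interval. Because Outcome measures gives flexion or abduction, the movement to be analysed has to be named for the model to be applied.
- **Sample size.** State whether 23° is the SD of ROM at a visit, and which visit, or the SD of the change. Only the investigators can say which. Tie the power statement to the baseline-adjusted analysis, giving the assumed correlation if one is relied on.

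**Cost:** an analysis amendment reported to the institutional review board, as Eligibility criteria requires for any protocol modification. No new data, visits or patients are needed: ROM is already measured at enrolment and at 12 weeks, and the planned SPSS software fits the model.
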